**Table 3 Tab3:**
[figure not shown]
Schedule of enrolment, interventions, and assessments

*Abbreviations*: *P* parent, *S* spouse, *C* child

### Data collection and outcome measures

Data collection will be conducted using software designed specifically for this study. Patients, spouses, children, and/or caregivers will complete assessments independently under the assistance of researchers.

This study has two primary outcomes, child mental health and parent–child communication. Child mental health will be measured using the strengths and difficulties questionnaire (SDQ) [12], a widely used measure with 25 items covering emotional symptoms, conduct problems, hyperactivity/inattention, peer relationship problems and prosocial behaviour. Parent–child communication will be measured using the parent-adolescent communication scale (PACS) [30], which has been previously used in children aged 7 and above [9] and comprises two subscales, open communication and communication problems, each with 10 questions. A significant improvement of either scale compared to the control group will be considered a positive result.

Secondary objectives will be assessed using the following measures:The 16-item version of the prodromal questionnaire (PQ-16) [15] will be used to assess the prodromal state in the child(ren). Child self-esteem will be assessed using the self-esteem scale (SES) [23].The clinical global impression scale (CGI) will be assessed by mental health professionals to reflect potential improvements in patient mental health.Parenting is a hypothesized mediating factors for the effect of LTC on parent–child communication. Parenting ability and stress will be measured using the parenting and mental illness scale (PMIS) [8] and the parental stress scale (PSS) [4], respectively.The final secondary objective of this study is to assess the cost effectiveness of LTC in China. To quantify utility, we will measure quality of life using the child health utility 9D (CHU9D) [25] in children and the brief World Health Organization quality of life scale (WHOQOL-BREF) [29] in patients.To provide preliminary information for future implementation of LTC, we designed 5 simple questions regarding current use of mental health services in patients.

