## Objectives

The primary objective of this study is to assess the efficacy of LTC in improving mental health of children of parents with schizophrenia or bipolar disorder in China. We hypothesize that the 3-session LTC intervention will result in improvements in child mental health or parent–child communication compared to a wait list control group.

The secondary objectives are to:Assess the efficacy of LTC in improving the mental health of parents experiencing schizophrenia or bipolar disorder.Explore potential mechanisms of action for improvement of child mental health using LTC. A proposed causal pathway is presented in Fig. 1.Assess the cost effectiveness of LTC in families with parental schizophrenia or bipolar disorder in China.

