### Sample size calculations

Sample size was calculated using SDQ as the primary outcome. Data from multiple countries (https://www.sdqinfo.org/g0.html) show that the population standard deviation of SDQ is roughly 5 points. Considering an SDQ difference of 3 points to be a clinically significant difference, at α = 0.05 and β = 0.9 levels, assuming a two-sided hypothesis and using 1:1 ratio of random allocation, the sample size needed for analysis is 120. As families with schizophrenia and bipolar disorder will be analysed separately, assuming a 40% dropout rate, 200 subjects will be needed for each diagnostic category. Therefore, 200 families with schizophrenia, and 200 with bipolar disorder will be enrolled.

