### Statistical analysis

Baseline categorical variables will be summarized as proportion of subjects with the count divided by the total number of evaluated subjects. Baseline continuous variables will be summarized as mean with standard deviation in case of normal distribution and as median with interquartile range in case of non-normal distribution. Efficacy will be assessed in the intention-to-treat population. Missing data will be imputed using the last observation carried forward method. Outcome variables will be differences between pre- and post-test scores at 50 days and 200 days.

Primary outcomes will be compared using t-tests if results conform to a normal distribution and nonparametric tests if they do not. Multivariate generalized linear regression models will be performed with outcome variables as the dependent variable, group allocation as the independent variable, and baseline variables as covariates to account for potential confounding. Data will be analysed as a whole and also separately in the two diagnosis groups. Further subgroups will be explored using interaction tests in the multivariate regression models. Potential subgroup identifiers include but are not limited to child mental health at baseline, parental disease severity, family socioeconomic status and child age. All inferences will be made at a significance level of α = 0.05.

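### Counting a positive trial on either SDQ or PACS, each at an undivided α = 0.05, roughly doubles the false-positive rate, and no primary time point or population is fixed to limit it further.

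*Protocol article*

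**What the plan says.** Under Data collection and outcome measures, the protocol article states: "This study has two primary outcomes, child mental health and parent–child communication". The first is measured by SDQ and the second by PACS. The same section gives the success rule: "A significant improvement of either scale compared to the control group will be considered a positive result". The Objectives section has the same either/or form, hypothesising "improvements in child mental health or parent–child communication compared to a wait list control group".

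The Statistical analysis section adds three statements:

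- On timing: "Outcome variables will be differences between pre- and post-test scores at 50 days and 200 days".
- On populations: "Data will be analysed as a whole and also separately in the two diagnosis groups".
- On the error rate: "All inferences will be made at a significance level of α = 0.05".

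Neither time point and none of the three populations is called primary. No alpha split, test order or correction is given.

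The Sample size calculations section uses one scale: "Sample size was calculated using SDQ as the primary outcome". It works at an undivided two-sided 0.05 and sizes each diagnosis for its own analysis: "As families with schizophrenia and bipolar disorder will be analysed separately, assuming a 40% dropout rate, 200 subjects will be needed for each diagnostic category".

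**The concern.** A rule that accepts success on either of two scales gives chance two opportunities. Testing each at the full 0.05 means the claim of efficacy does not carry the error rate the plan states. The plan is not silent here: it fixes both the either/or rule and the 0.05 for every inference, so a later document that split alpha would contradict it.

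The unranked time points and populations leave a second gap. The text does not make them part of the success rule, but nothing stops a result at one time point, or in one diagnosis, from being presented as the primary result.

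The stakes are practical. The Discussion says positive results would supply a treatment option for Chinese-speaking families and lead on to further cost-effectiveness work. It also concedes that the lack of blinding may inflate the apparent effect, which makes a loose success threshold harder to defend.

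**Working it through.** **Inputs from the document.** Two primary scales with an either-scale rule (Data collection and outcome measures). Two time points, three populations and α = 0.05 throughout (Statistical analysis). SD 5, difference 3, two-sided 0.05, 1:1 allocation, 120 analysable, 40% dropout (Sample size calculations). The power printed as β = 0.9 is read as 90%, since that is the reading that reproduces 120.

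**Assumed inputs.** The document gives no correlation between scales, between time points, or between baseline and follow-up. Ranges are used instead.

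**1. The plan's own figure.** n per arm = 2 × SD² × (z₀.₉₇₅ + z₀.₉₀)² / difference² = 2 × 25 × (1.960 + 1.282)² / 9 = 58.4, so 59. The exact t calculation gives 60 per arm, or 120. Dropout: 120 / (1 − 0.40) = 200 per diagnosis. The figure is reproduced, for one scale at an undivided 0.05.

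**2. Error rate of the explicit rule** (two scales, one time point, one population). With independent scales:

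- two-sided: 1 − 0.95² = 9.75%
- favouring LTC only: 1 − 0.975² = 4.94%, against 2.5% nominal

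With a correlation of 0.7 between the scales, the bivariate normal gives 8.3% and 4.2%. The rule counts only improvement, so the directional figure is the closer match to a false claim of benefit. Either way the rate is 1.7 to 2 times nominal.

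**3. If time points and populations could also support the claim.** Test statistics were simulated under the global null (1,000,000 draws). The two diagnosis groups are independent, and the whole-sample statistic is their equal-weight combination. Scale correlation runs from 0 to 0.7 and time correlation from 0.5 to 0.8.

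| Tests that could support the claim | Any p < 0.05, two-sided | Favouring LTC (nominal 2.5%) |
|---|---|---|
| 2 scales | 8-10% | 4-5% |
| 2 scales × 2 times, one group | 13-17% | 6.5-9% |
| 2 scales × 2 times × 3 populations = 12 | 27-36% | 14-19% |

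Setting both correlations to 0 gives 38.7% and 21.3% in the last row. The 46.0% for 12 independent tests cannot arise, because the whole sample contains the two groups.

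**4. Power once alpha is split.** Each figure is for the 3-point SDQ difference. The first three rows take SD 5 for the analysed score, as the plan does.

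| Setting | Power |
|---|---|
| 60 per arm, α = 0.05 | 90% |
| 60 per arm, α = 0.025 | 84% |
| Pooled sample, 120 per arm, α = 0.025 | 99% |
| 60 per arm, α = 0.025, baseline-adjusted, r = 0.3 / 0.5 / 0.7 | 88% / 93% / 99% |

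The last row uses a residual SD of 5 × √(1 − r²), that is 4.77, 4.33 and 3.57. To keep 90% power at 0.025 without adjustment needs 69 (z) to 71 (t) per arm. Enrolment would then be 138 / 0.6 = 230 to 142 / 0.6 = 237 per diagnosis, instead of 200.

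**The case against.** The strongest reply is that only the either-scale rule is written down. A reader might infer that the plan defines 12 routes to success, so that one significant PACS result at day 50 in bipolar families would make the trial positive and the error rate would be several times 5%. The document does not say so. It nowhere states that either time point, or any one population, suffices; it leaves them unranked at 0.05. This part of the reply stands: the 27-36% is an upper scenario, not the trial's error rate.

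A reader might also count the two PACS subscales and several informants as further routes. That is not supported. The subscales are described but not said to be tested separately. Who completes each primary scale is set out in Table 3, whose content is not available here.

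It can also be argued that the two diagnoses are separate questions, since each is sized for its own analysis, and need no correction across them. That is defensible if two separate conclusions are reported. It fails if success in either diagnosis makes the whole trial positive. Even with full control within each diagnosis, the chance of at least one false claim is then 1 − 0.95² = 9.75% two-sided, or about 5% favouring LTC.

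Lastly, Holm or Hochberg could be specified in an analysis plan not shown. Nothing in the article points to it, and it would conflict with the sentence on all inferences.

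**Conclusion.** The concern holds for the explicit rule. Accepting either SDQ or PACS at an undivided 0.05 gives about 8-10% two-sided, or 4-5% in favour of LTC against 2.5%, for scale correlations from 0.7 down to 0. That doubling follows from what the plan states and does not depend on how time points or populations are used.

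Anything larger is conditional. If both time points could support the claim in one group, the rate is about 13-17% (6.5-9% favouring LTC). If all 12 combinations could, it is about 27-36% (14-19%). These rest on assumed correlations and on a freedom the plan leaves open rather than asserts.

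It should be corrected before analysis, because it concerns the primary success criterion itself.

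**What to change.** 1. Name one primary time point and make the other secondary.
2. Fix the confirmatory population in one of two ways. Either the pooled sample is the single confirmatory population, or each diagnosis is a separate claim and the plan states that the trial as a whole is not called positive because one of them succeeds.
3. Within each confirmatory claim, test SDQ and PACS by Holm or Hochberg at an overall two-sided 0.05.
4. Make all other tests secondary, with no success claim attached.
5. Replace the sentence that puts all inferences at 0.05, and reword the either-scale rule to refer to the adjusted tests.

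**Cost.** With the pooled sample, this is wording only: about 120 analysable families per arm give about 99% power for the 3-point SDQ difference at 0.025.

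With separate diagnosis claims, the stated power must be revised. At 60 per arm it falls from 90% to 84%. This is the worst case under Holm, since SDQ is tested at 0.05 once PACS has passed at 0.025. Making the baseline-adjusted model the primary test, in place of the t-test on change, would give about 88%, 93% or 99% at assumed baseline/follow-up correlations of 0.3, 0.5 or 0.7. The plan already includes regression with baseline covariates, so this changes which analysis is primary and adds no new one. Without it, holding 90% would need 230-237 families enrolled per diagnosis.

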### Sample size calculations

Sample size was calculated using SDQ as the primary outcome. Data from multiple countries (https://www.sdqinfo.org/g0.html) show that the population standard deviation of SDQ is roughly 5 points. Considering an SDQ difference of 3 points to be a clinically significant difference, at α = 0.05 and β = 0.9 levels, assuming a two-sided hypothesis and using 1:1 ratio of random allocation, the sample size needed for analysis is 120. As families with schizophrenia and bipolar disorder will be analysed separately, assuming a 40% dropout rate, 200 subjects will be needed for each diagnostic category. Therefore, 200 families with schizophrenia, and 200 with bipolar disorder will be enrolled.

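### The sample size paragraph prints power as β, and its implied 90% matches the planned change-score test only if the unstated baseline-to-follow-up correlation is 0.5

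*Protocol article*

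**What the plan says.** The Sample size calculations section of the Protocol article bases the size on one of the two primary outcomes: "Sample size was calculated using SDQ as the primary outcome". Its inputs are an SD, "population standard deviation of SDQ is roughly 5 points"; an effect, "Considering an SDQ difference of 3 points to be a clinically significant difference"; and error rates, "at α = 0.05 and β = 0.9 levels, assuming a two-sided hypothesis". The result is "using 1:1 ratio of random allocation, the sample size needed for analysis is 120", which is inflated to 200 per diagnosis for 40% dropout because the two diagnoses are analysed separately.

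The Statistical analysis section then defines the analysis. On the outcome: "Outcome variables will be differences between pre- and post-test scores at 50 days and 200 days". On incomplete data, within an intention-to-treat population: "Missing data will be imputed using the last observation carried forward method". Primary outcomes are compared by t-test, or by a nonparametric test if the data are not normal. Regression models with baseline covariates are also planned. Every inference is at α = 0.05.

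**The concern.** β is the type II error rate, so the printed value describes a trial with a 10% chance of detecting a 3-point difference. That is false on the paragraph's own numbers, and it is the only power statement the protocol makes.

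The 90% that was evidently meant belongs to a comparison of single SDQ scores among 60 completers per arm. The planned primary test compares change scores among everyone randomised, with missing values carried forward. Both the variance and the expected mean difference can differ between these two analyses. Because each diagnosis group is sized separately, a null result in either group would be read against a 90% figure that the planned test may not have.

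**Working it through.** **Inputs.** From the protocol: difference 3, SD 5, two-sided α = 0.05, 1:1 allocation, 120 analysed, 40% dropout, 200 enrolled, all per diagnosis. Assumed, because the protocol gives neither: the baseline-to-follow-up correlation r and the timing of dropout. I also take the SD as 5 at every visit and the effect as 3 points at both follow-ups.

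**1. Reproducing 120 and 200.** With power 0.90:

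n per arm = 2·(1.960 + 1.2816)²·5²/3² = 58.4, rounded up to 59, or 118 in total.

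The exact t-test has 89.8% power at 59 per arm and 90.3% at 60, which gives 120. Then 120/(1 − 0.40) = 200. Both stated figures reproduce.

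With β = 0.9 taken literally (power 0.10):

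n per arm = 2·(1.960 − 1.2816)²·25/9 = 2.6, rounded up to 3, or 6 in total.

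Power 0.80 gives 88 in total, and one-sided testing at power 0.90 gives 96. Of the readings tried, only two-sided power 0.90 yields the stated figure.

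**2. Change score instead of single score.** SD(change) = 5·√(2(1−r)). Power is from the noncentral t distribution with 118 degrees of freedom and noncentrality 3/(SD·√(2/60)).

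| r (assumed) | SD of change | Noncentrality | Power, 60 per arm |
|---|---|---|---|
| 0.2 | 6.32 | 2.60 | 73% |
| 0.3 | 5.92 | 2.78 | 79% |
| 0.5 | 5.00 | 3.29 | 90% |
| 0.7 | 3.87 | 4.24 | 99% |

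The stated 90% is recovered only at r = 0.5.

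**3. All 200 with last observation carried forward.** In the worst case all 40% leave before day 50, so their change is zero.

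- Mean difference: 0.6 × 3 = 1.8, with 100 per arm.
- Variance of change: 0.6·SD² in the control arm and 0.6·SD² + 0.24·3² in the intervention arm.
- At r = 0.5: 15.00 and 17.16, average SD 4.01, standard error 4.01·√(2/100) = 0.567. Power ≈ Φ(1.8/0.567 − 1.96) = 89%.
- At r = 0.3: average SD 4.70, standard error 0.665. Power ≈ Φ(1.8/0.665 − 1.96) = 77%.

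Simulation agrees closely for the t-test and adds the rank test, which the normality rule could select given the spike of zeros:

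| Timing of the 40% loss | r | t-test | Rank test |
|---|---|---|---|
| All before day 50 | 0.5 | about 89% | about 82% |
| All before day 50 | 0.3 | about 79% | about 70% |
| Half before, half after day 50 | 0.5 | about 96% | about 94% |

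**4. Baseline-adjusted regression.** With baseline SDQ as a covariate the residual SD is 5·√(1−r²): 4.90 at r = 0.2 and 4.33 at r = 0.5. At 60 observed per arm, power is 91% and 96% respectively at α = 0.05, and 86% and 93% at α = 0.025.

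**The case against.** The firm error is one mislabelled symbol. N is right for 90% power and no design figure changes. That stands: a reader might infer from the printed β that the trial was sized for 10% power, but the 120 and 200 rule this out.

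The SD mismatch has no known direction. That also stands: power falls below 90% if r is below 0.5 and exceeds it if r is above. Concluding that the trial is underpowered would go beyond the protocol.

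The loss from carrying observations forward depends on early dropout, and the protocol gives no timing. Families lost after day 50 carry their day-50 value and are fully observed for the day-50 outcome. The 70% figure needs low r, all loss early and the rank test together. The figures in step 3 are therefore conditional, and at r = 0.5 the worst case barely moves the t-test.

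A reader might also infer that the 90% is overstated because the full 0.05 is spent on SDQ when success on either primary outcome counts. The documents do not support this. The plan tests each outcome at 0.05, so the sizing α matches it, and the chance of a positive result on either scale is at least the chance on SDQ alone. The either/or rule raises a type I error question (up to 1 − 0.95² = 9.75% if the two tests were independent), which is a separate matter.

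Finally, the plan already includes regression with baseline covariates and an analysis of both diagnoses together. If the covariates include baseline SDQ, which the text does not say, the regression largely removes the dependence on r. This supports the fix. It does not rescue the paragraph, which sizes each diagnosis separately and uses neither analysis.

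**Conclusion.** The printed β = 0.9 is wrong on the protocol's own numbers. It should read β = 0.10, and 120 and 200 are unaffected. This part is certain.

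The 90% is not established for the planned unadjusted test on change scores. It holds at r = 0.5, falls to 73% at r = 0.2 and rises to 99% at r = 0.7, assuming equal SDs of 5 at baseline and follow-up. Counting completers while analysing all randomised families adds a further dependence on dropout timing. At r = 0.5 the t-test ranges from about 89% (all loss before day 50) to about 96% (half the loss later). The size and direction of any discrepancy are unknown because r and the timing are not given. The point is worth correcting because this is the protocol's only power statement, but it is not evidence that the trial is too small.

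**What to change.** Rewrite the paragraph as follows.

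- Replace the printed β with power 1−β = 0.90 (β = 0.10).
- State that the SD of 5 is for a single SDQ score, and give the baseline-to-follow-up correlation assumed, with a range.
- Name the baseline-adjusted regression, with baseline SDQ as a covariate, as the analysis for which power is stated, using SD 5·√(1−r²). At 60 observed per arm and α = 0.05 this gives 91% to 96% for r = 0.2 to 0.5.
- Make clear whether power refers to the 120 observed or to all 200 with values carried forward. If carrying forward stays, add the assumed dropout timing. Simulation of the adjusted model on 100 per arm gives about 87% (r = 0.3) and 94% (r = 0.5) if all loss is before day 50, and about 97% and 99% if half is later.
- Only if α is split to control the either/or rule, also give power at 0.025: 86% to 93% for r = 0.2 to 0.5 at 60 observed per arm.

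The cost is one corrected paragraph, and the stated power may become slightly less favourable. No increase in enrolment is needed.

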### Statistical analysis

Baseline categorical variables will be summarized as proportion of subjects with the count divided by the total number of evaluated subjects. Baseline continuous variables will be summarized as mean with standard deviation in case of normal distribution and as median with interquartile range in case of non-normal distribution. Efficacy will be assessed in the intention-to-treat population. Missing data will be imputed using the last observation carried forward method. Outcome variables will be differences between pre- and post-test scores at 50 days and 200 days.

Primary outcomes will be compared using t-tests if results conform to a normal distribution and nonparametric tests if they do not. Multivariate generalized linear regression models will be performed with outcome variables as the dependent variable, group allocation as the independent variable, and baseline variables as covariates to account for potential confounding. Data will be analysed as a whole and also separately in the two diagnosis groups. Further subgroups will be explored using interaction tests in the multivariate regression models. Potential subgroup identifiers include but are not limited to child mental health at baseline, parental disease severity, family socioeconomic status and child age. All inferences will be made at a significance level of α = 0.05.

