### Follow up schedule

Data will be collected at baseline, 50 ± 5 and 200 ± 5 days after enrolment (around 1 and 6 months after the final LTC session). We chose to wait one month after the final session before collecting data to ensure subjects have time to apply skills and insights they gained from the intervention at home. Study staff will record demographic information during enrolment interviews. Patients, their spouses and their child(ren) will all be asked to complete questionnaires at baseline and follow-ups (see Table 3 for detailed schedule). When the primary caregiver of the child is not a parent, this primary caregiver will also be asked to complete the questionnaire.

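### Last observation carried forward is the only missing-data rule although 40% dropout is allowed for, and it can bias the change-score comparison in either direction

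*Protocol article*

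**What the plan says.** The Statistical analysis section of the protocol article fixes three things together. The population: "Efficacy will be assessed in the intention-to-treat population". The missing-data rule: "Missing data will be imputed using the last observation carried forward method". The outcome: "Outcome variables will be differences between pre- and post-test scores at 50 days and 200 days". No second method and no sensitivity analysis accompanies the rule.

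The Follow up schedule section gives three assessments: baseline, day 50 and day 200, the last two falling about 1 and 6 months after the final session.

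The Sample size calculations section takes an SD of 5 SDQ points and a difference of 3, and then, "assuming a 40% dropout rate, 200 subjects will be needed for each diagnostic category".

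The discontinuation criteria in Table 1 include psychiatric hospitalisation or an emergency visit by the patient, self-harm or aggression, and a new severe diagnosis in the spouse or a child.

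**The concern.** With one baseline and two follow-ups, carry-forward has only two possible effects on a change score. A family lost before day 50 has only its baseline value to carry, so its change is set to exactly zero at both visits. A family lost between the visits has its 1-month change entered as its 6-month change. If the 40% allowance is used up, 80 of the 200 families per diagnosis hold such a value in the day-200 analysis.

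The rule is not reliably conservative. It dilutes a lasting effect when loss is early. It keeps a faded effect alive when loss is late. When the arms lose families at different rates, it turns a change common to both arms into a difference between them. Unequal loss is plausible because the trial is unmasked with a wait-list control. Several discontinuation criteria are also bound up with family deterioration. If assessment stops at such an event, the carried value is the score from before it.

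**Working it through.** **Inputs from the article.** Difference 3 ("Considering an SDQ difference of 3 points to be a clinically significant difference"), SD 5 ("the population standard deviation of SDQ is roughly 5 points"), two-sided α = 0.05, 1:1 allocation, 40% dropout. The article writes "at α = 0.05 and β = 0.9 levels", read here as 90% power.

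**The plan's own figure.** n per arm = 2 × (1.96 + 1.2816)² × 5² / 3² = 58.4, so 59 per arm and 118 in total. With the t distribution it is 59.35, so 60 per arm and 120 in total. 120 / (1 − 0.40) = 200. The stated 120 and 200 both reproduce. This inflation treats 120 families with observed data as the analysed set, whereas carry-forward analyses all 200.

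**Inputs assumed, because the article does not give them.** The share lost before day 50 (*e*), the split of dropout by arm, the course of the effect, the mean change in the control arm, and a correlation of 0.5 between assessments (so the SD of a change is also 5). Simulations use 100 families per arm (one diagnosis), 4,000 replicates, dropout unrelated to outcome, and a t-test on change. Improvement is counted as positive. The comparator is a baseline-adjusted regression on observed day-200 scores.

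**(a) Equal 40% dropout.** Estimate at day 200 = 0.6 × (day-200 effect) + (0.4 − *e*) × (day-50 effect).

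For a constant effect of 3:

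| Lost before day 50 | Lost after day 50 | Estimate |
|---|---|---|
| 0% | 40% | 1.8 + 1.2 = 3.0 |
| 10% | 30% | 1.8 + 0.9 = 2.7 |
| 20% | 20% | 1.8 + 0.6 = 2.4 |
| 30% | 10% | 1.8 + 0.3 = 2.1 |
| 40% | 0% | 1.8 + 0 = 1.8 |

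Simulation agrees (1.81 with all loss early, about 2.4 at 20%/20%). The effect is detected in about 89% of trials with all loss early, 96% at 20%/20% and 98% at 10%/30%, against about 96% for the comparator.

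**(b) Effect of 3 at day 50, none at day 200.** The estimate reduces to (0.4 − *e*) × 3, where the truth is 0.

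| Early / late loss | Estimate | Significant (simulated) |
|---|---|---|
| 20% / 20% | 0.6 | about 15% |
| 10% / 30% | 0.9 | about 26% |
| 0% / 40% | 1.2 | about 40% |

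The comparator stays at about 5%.

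**(c) No effect, both arms improve by 2 points, dropout 30% in one arm and 50% in the other.**
- All loss before day 50: 0.7 × 2 − 0.5 × 2 = 0.4 point in favour of the arm with less dropout; type I error about 10%.
- Loss split evenly between early and late: 0.85 × 2 − 0.75 × 2 = 0.2 point; type I error about 6–7%.

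**(d) Standard error.** With all loss early, the mean t-test standard error was 0.565 against an empirical SD of the estimates of 0.559 to 0.568. At 20%/20% it was 0.642 against 0.646 to 0.649. With no effect and equal dropout, the type I error was 4.8–5.4%.

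**The case against.** The strongest reply is that every size above rests on assumptions, some of them at an extreme. That stands in several respects.

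- The 40% is an inflation allowance, not a forecast, and the article says nothing about when families leave. The value 1.8 needs every loss to fall before day 50.
- Scenario (b) needs the effect to vanish completely and concerns only day 200. With half the effect left (1.5) and 20%/20% loss, the formula gives 0.9 + 0.6 = 1.5, so the two errors cancel.
- Scenario (c) reaches 10% only if all loss is early.
- Calling 3 the true effect assumes that families lost early would have had the full benefit. The sessions run over a month, so some may not have completed them, and their effect under an intention-to-treat question may be smaller.
- The comparator's 5% follows from making dropout unrelated to outcome. It does not show that an observed-data analysis is safe in this trial.

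A reader might also infer that carried values treated as observed make the standard error too small, or that the rule decides the trial's result. Neither is supported. The standard errors in (d) match the spread of the estimates, and a constant 3-point effect is still found in about 89% of trials or more, partly because imputed zeros also reduce the SD.

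The objection does not remove the core point. The rule is stated, it is the only one, and its bias can go either way. An analysis plan not shown here could add detail, but the method named in the article is already fixed.

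**Conclusion.** The concern holds as one of bias in the estimated effect and, where dropout is unequal or an effect fades, in the test. With equal 40% dropout and a constant 3-point effect, the day-200 estimate lies between 3.0 and 1.8. A day-50 effect that has gone by day 200 is still reported as about 0.6 to 1.2 points when 20% to 40% of families are lost after day 50, and is significant in about 15–40% of trials. With no effect, a common 2-point improvement and 30% versus 50% dropout, the bias is about 0.2 to 0.4 point and the type I error about 6–10%.

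The value 1.8 should not be read as the expected result, nor as a floor. With 50% early dropout under intervention, 30% under control, and a control-arm improvement of 2 points, the estimate is 0.5 × 5 − 0.7 × 2 = 1.1. Power loss is secondary: about 89% against 96% in the all-early case. All these sizes rest on the assumed dropout timing, arm split, effect course and correlation. Because the rule governs the primary outcomes and is cheap to replace, it should be changed before outcomes are examined by arm.

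**What to change.** Replace carry-forward as the primary method with one of two options:

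- multiple imputation by arm, using baseline and both follow-up visits; or
- a likelihood-based repeated-measures model of the day-50 and day-200 scores, with arm × visit, baseline × visit, centre and diagnosis.

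If the second is chosen, note that with baseline as a covariate a family with no follow-up score contributes nothing. That is the very group behind the 1.8, so such a model cannot be described as using all randomised families. Put baseline in the response vector if those families are to be included.

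Both options assume data missing at random. Because several discontinuation criteria are related to outcome, pre-specify one not-at-random sensitivity analysis: control-based imputation or a delta tipping point. Keep carry-forward at most as a further sensitivity analysis.

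The cost is a change of wording and modest programming, with no new data or families. The price is reliance on the missing-at-random assumption, which the sensitivity analysis is there to test. The article plans no interim analysis, so the change can be made without knowledge of results by arm.
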